## Abstract

**Background:**

The focus of this project is on improving the provision of primary palliative care (PC) by general practitioners (GPs). While approximately 10–15% of the incurable, seriously ill or dying people will be in need of specialist PC, the vast majority can be adequately treated within generalist care. The strengthening of the GP’s role in PC, as well as ensuring close collaboration between specialist PC services and GPs have been identified as top priorities for the improvement of PC in Germany. Despite healthcare policy actions, diverse obstacles still exist to successful implementation of primary PC on a structural, process, and economic level. Therefore, this project aims at addressing barriers and facilitators to primary PC delivery in general practice in Germany.

**Methods:**

The study follows a three-step approach; first, it aims at systematically analyzing barriers and facilitators to primary PC provision by GPs. Second, based on these outcomes, a tailored intervention package will be developed to enhance the provision of primary PC by GPs. Third, the intervention package will be implemented and evaluated in practice. The expected outcome will be an evidence-based model for successful implementation of primary PC delivery tailored to the German healthcare system, followed by a strategic action plan on how to improve current practice both on a local level and nationally.

**Discussion:**

The first step of the project has been partly completed at the time of writing. The chosen methodologies of four sub-projects within this first step have opened up different advantages and disadvantages for the data collection. In sum of all sub-projects, the different methodologies and target groups contributed valuable information to the systematic analysis of barriers and facilitators to primary PC provision by GPs.

**Trial registration:**

The study (BMBF-FK 01 GY 1610) was retrospectively registered at the German Clinical Trials Register (Deutsches Register Klinischer Studien) (Registration N° DRKS00011821; date of registration: December 04th 2017) and at the German Register of health care research (Versorgungsforschung Deutschland - Datenbank) (Registration N° VfD_ALLPRAX_16_003817; date of registration: March 30th 2017).

## Background

In Germany, as in many other high-income countries, it is anticipated that both the proportion and the actual numbers of people who should receive palliative care (PC) is increasing considerably [1–3]. The remit of PC has expanded since its relevance for other diseases than cancer has been widely acknowledged; in addition, integration of PC at an earlier stage in the disease process – not only close to death – has been shown to be beneficial [2]. In addition, the demand in primary care will rise with an ageing population and changing patterns of mortality – people at older ages often suffer from multiple chronic diseases of indeterminate prognosis [4]. According to estimates by the German Association for Palliative Medicine (DGP), up to 90% of the approximately 850,000 people who die in Germany each year will be in need of PC [3]. Of those, about 10% will require specialist PC at some point, while the majority will need primary PC. It is estimated that general practitioners (GPs) on average care for 3–4 patients with PC needs per quarter; however, these figures presumably underestimate the real care extent since these estimates do not appropriately reflect care for patients with non-oncological conditions [5]. The situation of patients in need of PC in a general practice is characterized by multi-morbid patients with a broad spectrum of conditions and a predominance of non-oncological chronic diseases such as cardiovascular or pulmonary diseases [6]. From a public health perspective, these trends demand for new approaches to service delivery; research into models for successful implementation of primary PC is therefore paramount.

### International evidence base regarding primary palliative care

Primary PC can be defined as “the clinical management and care coordination including assessment, triage, and referral using a palliative approach for patients with uncomplicated needs associated with a life limiting illness and/or end of life care. Has formal links with a specialist palliative care provider for purposes of referral, consultation and access to specialist care as necessary” [7]. Evidence from international research consistently underlines the importance of PC in a generalist setting as an indispensable element in the continuum of care provision, as well as the pivotal role of the GP in the provision of primary PC [8, 9]. In a number of countries, the fundamental right for patients of all diagnoses to receive PC from an early point in the course of a life-limiting condition is now anchored in policy and legislation, involving an increased emphasis upon the role of primary PC [2]. It has been argued that a wise combination of generalist and specialist PC constitutes a more sustainable and cost-effective approach to care provision [10]. Accordingly, in the past decade, important scientific, policy and advocacy initiatives were developed internationally to facilitate primary PC provision by GPs and to support their endeavors [11–14].

### Challenges related to the provision of primary palliative care in general practice

Despite the widely acknowledged importance of GPs’ engagement in primary PC [11], a number of - partly interrelated - challenges were identified related to the delivery of primary PC in practice; these concern 1) structural barriers (e.g. GP undersupply and uneven distribution in rural versus urban areas), knowledge barriers (e.g. lack of knowledge, skills, and clinical routine in providing PC; practical obstacles to undertake training), 2) service barriers (e.g. lack of active GP involvement in transition from curative to PC), and 3) consequences of the “specialization” of PC (e.g. unclear role definitions and lack of clarity regarding roles and responsibilities of generalist PC and communication and collaboration between generalist and specialist care providers) [2, 15].

### German context

Position papers and professional guidelines by leading authorities [16, 17], as well as nationwide consented public health actions to improve PC provision in Germany [18], define generalist PC as the foundation of all PC concepts and emphasize the pivotal role of the GP in PC delivery. Research confirmed that GPs in Germany regard it as their responsibility and as part of their professional self-perception to care for their patients throughout the whole disease trajectory, including provision of end-of-life care. The crucial importance of strengthening PC by GPs was even anchored in the ‘hospice and palliative care law’ passed in 2015 [19]. However, to date it has not been clearly defined what PC in general practice exactly entails [20]. The clinical guideline for PC for cancer patients [16] details generalist PC as follows: palliative basis and follow-up assessment of the patient’s status; the treatment of symptoms of low to medium complexity; involvement of specialist PC if appropriate; and identification of treatment goals in agreement with the patient. The ideal situation described in the law and in the clinical guideline is, however, far from being implemented into practice, and a pronounced undersupply of patients with generalist PC has been stated [3]. Routine data of health insurances indicate that primary PC occurs too late in the course of a life-limiting disease, and predominantly for patients with oncological diseases, confirming the still prevailing idea among GPs that PC is primarily applicable close to a patient’s death and in the context of cancer care [3]. Until now, the regulatory framework for primary PC delivered by GPs merely consists of four specific billing codes introduced in the medical compensation system in 2013, while not allowing for statements regarding the quality of the care provided. In addition, the codes only refer to single services by GPs, while nursing and other care is not included. This is critically discussed since these billing codes do not ensure essential features of holistic PC provision such as coordination, network structures, and multi-professional care. Particularly the team approach, a key element of successful and sustainable PC provision, is not adequately considered in the current regulations for primary care. Unlike with specialist palliative home care, where conditions, admission criteria, and care activities have been defined, for generalist palliative care this is very vague, bearing confusion and uncertainties for professionals, patients and families, as well as other involved stakeholders [20]. The intent to strengthen primary PC economically by improving remuneration for services delivered by primary care providers was recently anchored in law [19]. However, until now, no systematic approaches for the practical implementation of these innovations are in place, and empirical evidence on costs and benefits of respective care models is lacking.

GPs providing PC in Germany are confronted with the difficulty of integrating the demands of end of life care with a generalist caseload that usually implies many competing priorities [2, 21, 22]. In international comparison, physicians in Germany showed the highest self-assessed workload and the greatest number of patient contacts, with at the same time the shortest time per patient contact of only 9.1 min [23]. There is a tension between a pressurized context of care [2] and the nature of PC work with its unpredictable demands, uncertainty of illness trajectory, and its difficulty in planning, its intensiveness, and its personal strains [21]. Interactions with patients in the context of PC provision tend to require high investment of time, communicative and emotional effort, and tolerance towards uncertain outcomes. These requirements can become incompatible with the other demands on a GP in his or her every day practice [24]. For example, frequent and time-consuming home visits may be difficult to cope with in a regular every day practice characterized by high workload and time pressure. In addition, depending on the regional or local care infrastructure, GPs often feel as “lone fighters” in providing PC for their patients, while team composition and access to specialist support were emphasized as crucial for the capacity to provide PC in a generalist setting [22].

In summary, a first foundation of research [6, 24], education and professional guidance [16, 25], and policy initiatives [17, 19] has been laid for enhancing primary PC delivery in Germany. However, the scientific evidence base and the conceptual development are not as far advanced as in countries such as the UK, the Netherlands, or Australia. To date, a comprehensive program for enhancing primary PC has not been developed. Although core findings and recommendations from other countries may be partly transferrable, the concrete practice largely depends on the particular conditions of the national healthcare system and structural prerequisites in the regional context of healthcare provision, with implications for the role and responsibility of the GP in the provision of care.

## Aim and research question

This research project aims at providing an empirical basis for the sustainable implementation of primary PC by GPs. Sub-goals are:the systematic analysis of barriers and facilitators to primary PC provision using a theoretical framework from implementation science,the development of a tailored intervention package to enhance primary PC provision and support care providers to integrate the new processes with their everyday practice, andthe implementation and evaluation of the intervention package to assess its practical applicability and its effects on patient care.

### Research questions

I.Analysis and operationalization of barriers to primary PC provision by GPs in the German healthcare context on a structural, educational, process, and economic level: Which mechanisms and formal regulations impede routine embedding of PC provision in GPs everyday clinical practice at individual and collective level?II.Identification and operationalization of concrete measurable actions to improve the implementation of primary PC delivery by GPs: Which measures will have the potential to facilitate integration of end of life care with a generalist caseload and to enable the GP and his practice team to provide high quality PC to their patients? Which measures will be suitable to promote collaboration with other care providers relevant for PC delivery?III.Testing and evaluation of a tailored intervention package for the facilitation of primary PC delivery by GPs in Germany: What is its practicality, as well as its impact on care and patient-relevant outcomes? How well does it score compared to other models of GP involvement in PC delivery?

## Methods and design

To ensure scientific quality and rigor, the study design was developed in line with the recommendations for organizational health services research and theoretical foundation of health services research by the German Network for Health Services Research [26, 27]. The study encompasses three phases modelled after the framework for the development and evaluation of tailored interventions by Campbell et al. [26] (Fig. 1).The *theoretical phase* of this research is designed to gain an in-depth understanding of the mechanisms that determine the (un)successful delivery of primary PC in general practice.The *modelling phase* uses participatory methods and consensus building techniques in order to ensure ownership of the resulting intervention package and hereby enhance advocacy, dissemination, and the likelihood that the intervention will be successfully implemented into practice on the long term.The *implementation and evaluation phase* is designed to test and evaluate the acceptance, feasibility, and applicability of the intervention package in practice. Using formative evaluation, it will be examined how the individuals and groups involved in the delivery of primary PC engage in the mobilization of resources to secure consent, trust, and cooperation, as well as in the realization of activities that may lead to routine incorporation of elements of practice into everyday work. Summative evaluation will be employed to assess the outcomes in terms of the quality of patient care, the costs and benefits for the involved stakeholders, and the impact of the intervention package for the healthcare system.

**Fig. 1 Fig1:**
[figure not shown]
Design of the research project, modelled after Campbell et al. [26, 27]

### Study population and data collection

***Phase I – Theoretical Phase:*** The theoretical phase comprises four sub-projects.

First, an *organizational ethnographic field approach* will be applied to gain insights into the practices involved in delivering primary PC and to analyze barriers and facilitators. Data will be collected by means of document analysis (such as care plans, case notes, registers); by work shadowing (observation of daily routines, team meetings, staff interactions, home visits); and by interaction with staff (informal interviews, cognitive interviewing / think-aloud technique) [28]. Field notes will be taken according to a pre-defined scheme [29] and will be transformed into accounts including information about procedures, observations of actions and interactions, quotations of conversations, interpretations (e.g. of underlying attitudes), and the researcher’s intuitive thoughts and memos. These accounts will be imported into data files using software for qualitative text analysis (MaxQDA®).

*Second, a secondary analysis of qualitative data* [30] will be undertaken with a particular focus on barriers and facilitators of PC provision by GPs. Data are available from a recently concluded project on end of life care for frail older patients in family practice (ELFOP), a longitudinal study on needs, appropriateness and utilization of services (funding number: BMBF-FK 01 GY 1120) funded by the Federal Ministry of Education and Research. Participants were selected through theoretical sampling to include GPs with different backgrounds, working conditions (single or joint practice), and working in rural and urban areas characterized by diverse care infrastructures. Both the interviews and the group discussion include relevant information on the GPs’ perception of tasks, problems, challenges in the end-of-life care for frail older people, as well as on their perceived roles, responsibilities, and professional self-perception within this context of care.

Third, based on the findings from ethnographic research and secondary interview analysis focused interviews will be conducted with GPs, GP assistants or nurses from home care teams or inpatient service provider, patients, and their relatives (Table 1) using the *Critical Incident Technique* (CIT) [31, 32] to identify significant mechanisms that result in excellent practice versus in undesirable or even harmful events.

**Table 1 Tab1:** Target/ study population detailed for each work package of data collection

Work package	Target population	Proposed sample size	Sampling strategy
Ethnographic research	GPs; GPs assistants, professional caregivers	*n* = 30	The Institute of General Practice’s education and research network of *n* = 250 general practices; theoretical sampling contrasting: rural vs. urban; single vs. joint practice; specific palliative education vs. nonspecific palliative education
Secondary analysis	GPs, GPs assistants, professional caregivers	interviews: *n* = 52 group discussions: *n* = 3	Existing data set of interviews / one focus group with GPs conducted within the ELFOP project; all interviews and the focus group are included
CIT	GPs, GPs assistants, professional caregivers, patients and relatives	*n* = 16	Theoretical sampling contrasting: rural vs. urban; diagnosis; single vs. joint practice; men vs. women
Analysis of Health insurance claims data	GPs’ patients identified as being in need of PC	not applicable	Health insurance claims data: all AOKN and BARMAR insured persons in Lower Saxony with palliative billing codes
PAR	GPs, community nursing teams, patients and informal carers, other relevant PC providers	not applicable	Theory-based purposive sampling [55]
Delphi study	GPs’ professional representatives and other relevant experts for health policy decision making and healthcare planning	*n* = 30	DEGAM; DGP; GPs’ chairmen / quality circles; the Institute of General Practice’s close links with GPs’ professional boards and associations (Hausärzteverband)
Consensus workshops	GPs’ professional representatives; health insurers; experts for medical education; and other relevant experts for health policy decision making and healthcare planning	*n* = 20	Two groups with approximately 10 participants each; theory-based purposive sampling [55]
Implementation of the intervention package	GPs’, community nursing teams, health insurers; and other relevant experts for health policy decision making and healthcare planning	not applicable	Exemplary test region in Germany (Lower Saxony) involving n = 8 general practices, as well as all relevant service providers and stakeholders in the respective region
Questionnaire survey (Summative evaluation)	GPs’, community nursing teams, health insurers; and other relevant experts for health policy decision making and healthcare planning	*n* = 130	Service providers, insurers, and other local stakeholders involved in the implementation of the tailored intervention package (Phase II) and from two exemplary other regions in Germany
Patient-relevant outcomes (Summative evaluation)	Patients and informal carers	standardized scales *n* = 32 interviews *n* = 16	Patients and informal carers attended by general practices who are involved in the implementation of the tailored intervention package (Phase II) and from two exemplary other regions in Germany

Fourth, *secondary analysis of health insurance claims data* of the AOK – Die Gesundheitskasse für Niedersachsen (AOKN, statutory health insurance) and BARMER (statutory health insurance), and from the GPs’ office software will serve to describe the morbidity and service usage of patients, assess patient-relevant outcomes such as hospital admissions, estimate the time investment and costs for the provision of primary PC by GPs, and to draw inferences on the relevant laws, professional regulations, and reimbursement systems (see Table 2).

**Table 2 Tab2:** Outcomes, comparators, and data sources

Outcome	Measure(s), indicator(s)	Data source
Patient-related outcomes		
Quality of life	Physical and psychosocial wellbeing, social support, financial strain	Standardized quality of health / care related measures such as POS^a^; QODD^b^; QUELC^c^
Quality of care	Unplanned hospital admissions	Health insurance claims data
Service usage and time investment		
Service usage	GPs’ consultations and home visits; prescriptions (medication, medical aids, interventions); referral to specialists and other service providers; out-of-hours contacts; emergency interventions	Health insurance claims data GP’s office software
GPs’ time investment	Time dedicated to assessments, home visits, telephone consultations, physical care, and psychosocial care	Time registration (ethnographic field research)
Impact on GPs’ and practice staff’s ability and capacity to deliver primary palliative care		
Quality of palliative care delivery	GPs’ and practice staff’s appraisal of the quality of PC provided to their patients	Organizational ethnographic field research including individual and group interviews
Quality of care other than palliative care	GPs’ and practice staff’s appraisal of the quality of care provided to other patients	Organizational ethnographic field research including individual and group interviews
Work satisfaction	GPs’ and practice staff’s work-related satisfaction and sense of meaningfulness	Organizational ethnographic field research including individual and group interviews
Economic evaluation		
Direct costs for the healthcare system	Service usage (consultations and home visits, prescriptions of medicines and medical aids, specialist referrals, social services, out-of-hours contacts, emergency interventions)	Health insurance claims data GP’s office software
Direct costs for patients and relatives	Additional costs for medications and therapeutic interventions not covered by the health insurance funds	Organizational ethnographic field research including individual and group interviews
Indirect costs for patients and relatives	Social isolation; (temporary) work loss; abandon of activities or relationships	Organizational ethnographic field research including individual and group interviews
Direct costs for GPs and other healthcare providers	Costs invested for PC not remunerated within the medical compensation system	Organizational ethnographic field research including individual and group interviews
Indirect costs for GPs and other healthcare providers	Personal strain; impact on healthcare professionals’ private lives; abandon of activities or relationships	Organizational ethnographic field research including individual and group interviews
Feasibility of the intervention package		
Process monitoring and formative evaluation of the implementation phase	Normalization Process Theory core constructs (coherence, cognitive participation, collective action, and reflexive monitoring)	NoMAD^d^ assessment instrument for the evaluation of the implementation of complex interventions

^a^Palliative Outcome Scale [38]

^b^Quality of Dying and Death questionnaire [47]

^c^Quality of End of Life Care Questionnaire [55]

^d^Measure Development Based on Normalization Process Theory [56]

***Phase II – Modelling Phase:*** The modelling phase consists of three sub-projects building up on each other.

First, *Participatory Action Research* (PAR) [33] will be undertaken with general practices, community nursing teams, patients and informal carers, as well as other relevant PC service providers to define adequate operationalization of PC processes and quality outcomes, and to condense a set of service development statements [34, 35].

Second, a *nation-wide consensus Delphi study* will be undertaken with GPs and their professional representatives such as the GPs’ professional federation, the Medical Chamber, and the German association of general practice (DEGAM) to seek expert consensus on these service development statements.

Third, *consensus workshops* will be conducted in the follow-up of the *Delphi study*, using the *Nominal Group Technique* [36] to elaborate a strategic action plan on how to put the service development statements into practice. Workshop participants will be key representatives from the practical, education, economic, and policy sphere, as well as representatives of patients and relatives. Data collected during this phase will be integrated during analysis (see [2, 37]) to design the tailored intervention package.

Finally, an intervention package will be developed for enhancing the integration of PC provision into general practice, drawing on the example of the Gold Standards Framework for Palliative Care [12], but adapting it to the German context. A participatory framework and consensus building techniques will be applied to promote ownership of the developed elements and to enhance commitment among the relevant stakeholders.

***Phase III – Implementation and evaluation:*** The intervention package developed in phase II will be implemented and evaluated in an exemplary test region in Lower Saxony.

First, *formative evaluation* will use an organizational ethnographic approach including individual and group interviews with relevant stakeholders to (a) test the feasibility and acceptance of the intervention in practice, and (b) to compare the intervention to two exemplary other regions in Germany with different approaches to generalist and specialist PC provision in terms of contracts with health insurance funds, different roles of GPs in the local delivery of PC (e.g. Westphalia-Lippe).

Second, *summative evaluation* will be accomplished to assess the effects of the intervention on patient care in terms of physical, practical, and psychological outcomes. Data sources will be a questionnaire survey among the relevant stakeholders involved in PC provision; analysis of clinical and health insurance funds routine data to assess the effects on patient care, service usage, and costs of care; and perceptions of patients and relatives regarding the outcomes of care using established instruments such as the Palliative Outcome Scale [38] (Table 2).

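### The direct healthcare-system cost in Table 2 leaves out inpatient stays, so the cost comparison misses any change in hospital cost and could reverse sign

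*Protocol article*

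**What the plan says.** Under Economic evaluation, Table 2 gives one measure for direct costs to the healthcare system: "Service usage (consultations and home visits, prescriptions of medicines and medical aids, specialist referrals, social services, out-of-hours contacts, emergency interventions". The data sources are health insurance claims data and the GP's office software.

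Table 2 also has a separate outcome row named Service usage, with the same two sources. Its measure is "GPs’ consultations and home visits; prescriptions (medication, medical aids, interventions); referral to specialists and other service providers; out-of-hours contacts; emergency interventions".

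Hospital use enters Table 2 once, in the Quality of care row, as "Unplanned hospital admissions", taken from claims data. The Phase I text on the claims analysis likewise treats it as an outcome; it will "assess patient-relevant outcomes such as hospital admissions".

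The scope promised for the evaluation is wide. In Methods and design, the summative evaluation covers "the costs and benefits for the involved stakeholders, and the impact of the intervention package for the healthcare system". In Study population and data collection, Phase III, it includes "analysis of clinical and health insurance funds routine data to assess the effects on patient care, service usage, and costs of care", in a sentence that ends by pointing to Table 2.

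**The concern.** The label of the cost outcome and its content do not agree. A cost to the healthcare system would be expected to include hospital care, particularly for seriously ill and dying patients and in a project that takes unplanned admissions as its indicator of care quality. The listed components are mostly ambulatory. If better primary palliative care avoids some hospital stays, whatever it adds in GP work is counted and what it saves on inpatient care is not.

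The article says in its German context section that empirical evidence on costs and benefits of such care models is lacking. Under Dissemination and implementation it plans summaries for health insurance funds and policy makers. A partial total carrying a full-system label could mislead those readers. It could also sit awkwardly beside a fall in admissions taken from the same claims data.

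**Working it through.** The plan states no cost figure, so there is nothing to reproduce. The check has two parts.

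**1. Item-by-item comparison of the two Table 2 lists**

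| Item | Direct-cost row | Service usage row |
|---|---|---|
| Consultations and home visits | yes | yes |
| Medicines and medical aids | yes | yes |
| Prescribed interventions | no | yes |
| Referral to specialists | yes | yes |
| Referral to other service providers | no | yes |
| Social services | yes | no |
| Out-of-hours contacts | yes | yes |
| Emergency interventions (undefined) | yes | yes |
| Inpatient hospital stays | no | no |

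The cost row calls its measure service usage, but its list differs from the row of that name in three items. Neither list has inpatient stays. Nor does the cost list carry a phrase that marks it as illustrative, although Table 2 uses such a phrase in its Quality of life row. No other part of the article says that inpatient stays are costed.

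**2. Effect of the omission on the cost difference**

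The documents give no costs, so the quantities stay as symbols, each a change per patient under the package:

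- g = added GP and community cost (in the list)
- e = saved out-of-hours and emergency cost (in the list)
- h = saved inpatient cost (not in the list)

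Change by the Table 2 list: g − e.

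Change with inpatient care included: g − e − h.

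Error of the Table 2 list: (g − e) − (g − e − h) = h.

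If stays are avoided, h > 0 and the list overstates the cost change by exactly h. If inpatient cost rises, h < 0 and the list understates it by the same rule. For h > 0 there are three cases:

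- g ≤ e: the list shows no rise. It understates the saving, but the direction is not wrong.
- e < g < e + h: the list shows a rise while the full cost falls. The sign is reversed.
- g ≥ e + h: the list shows a rise and the full count shows no saving either. The rise is overstated but not false.

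So the direction of the bias follows from the omission, while a reversed sign needs the middle case.

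**The case against.** The strongest reply is that this is a journal article, and that detailed cost components, pricing and perspective usually belong to a fuller document that is not shown. That would answer a complaint about missing detail. It does not answer this one, because the article does fix a component list, and that list does not support the outcome's label.

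Several other objections stand and limit the point.

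- A reader might infer that the protocol defines its cost outcome inconsistently across sections. The documents do not support this. The phrases in Methods and design and in the Phase III text list no components, so they cannot conflict with Table 2. The Phase I aim to "assess patient-relevant outcomes such as hospital admissions, estimate the time investment and costs for the provision of primary PC by GPs" concerns GP provision before any package exists, and it may properly be narrower.
- A reader might infer that a package shifting care from hospital to GP would be reported as raising costs. That does not follow. Out-of-hours contacts and emergency interventions are counted and may offset the added GP cost. The package had also not been designed at the time of writing, and no passage says that it is meant to increase consultations, home visits or prescriptions.
- Unplanned admissions are reported separately, so a fall would be visible. It would still not be valued in the cost total.
- Emergency interventions might cover some hospital care. Because the term is undefined, it cannot be relied on to fill the gap.
- The implementation involves 8 general practices, the article states no hypothesis test or decision rule on cost, and statistical results are to be set against qualitative cost data. This lowers the stakes but does not correct the total.

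**Conclusion.** The point holds in a limited form. As written, the direct healthcare-system cost omits inpatient stays, and the cost comparison is therefore wrong by the full value of any change in inpatient cost. If the package reduces hospital stays, the error runs against it, and the sign could reverse when e < g < e + h.

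That condition is as far as the size can be taken. The documents give no unit costs and no expected number of avoided stays, so any euro figure would only reflect the values chosen for it. The conclusion assumes that the Table 2 list is applied as it stands and that emergency interventions do not already include inpatient care.

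The mismatch between the two service-usage lists is real but secondary: it affects which items are counted, and neither version includes hospital stays.

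**What to change.** Four changes to Table 2 and the matching text:

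1. Add inpatient hospital stays, planned and unplanned, costed from the claims data, to the direct healthcare-system cost row.
2. Define emergency interventions so that hospital care is not counted twice.
3. Use one component list for the Service usage row and the cost row, settling whether social services, prescribed interventions and other service providers belong in both.
4. If inpatient costs cannot be obtained, relabel the outcome as ambulatory or primary-care cost and do not present it as cost to the healthcare system.

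The cost is some rewording and one more cost item from claims data already used for admissions. The article does not list the fields requested, and its Discussion reports that contracts, data protection and data transfer took longer than planned, so the extra item may not come free; the fourth change covers that case. Inpatient costs are skewed, so the interval around the cost difference will be wider.
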